## Randomization and blinding/masking

Randomization will take place in July 2016, after recruitment and baseline interviews. Randomization will be stratified by district. For each of 6 areas (each area corresponding to 2 districts) approximately 1000 allocations of the clusters will be computer-generated by an independent scientist tasked by CISMAC. Each allocation will be numbered. We will organize six randomization ceremonies where schools will be randomly allocated to one of the three trial arms. Officials from the study districts, head teachers and PTA chairpersons of the trial schools and chiefs will be invited to be present, and others, including community members, will be welcome to come too. Tickets will be drawn from a box with numbers corresponding to a specific allocation of clusters to the three arms.

There will be no blinding of participants, but the team doing the final survey will be independent from the intervention delivery and efforts will be put in place to keep them unaware of the intervention/control status of respondents. Biannual follow-up contacts with the participants and the final surveys will be conducted by an independent team of research assistants, most of them located in Lusaka.

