Proportions will be compared on both absolute and relative scales. Thus, relative risk, RR (and its analogue effectiveness, 1-RR) and absolute risk reduction (and its reciprocal “Numbers needed to prevent”) and their 95% CIs will be estimated using generalized linear models (GLM) of the binomial family with a log link and identity link, respectively. We will also employ logistic regression to arrive at ORs for the binary outcomes. Cox regression analyses will be used for estimating the effect of our interventions on time to first pregnancy. We will in all the analyses account for the cluster effect using robust standard errors. Random effects models will be used to assess population effects whereas fixed effects models will be used to assess individual effects. We will check whether the model fit is good by comparing the estimates from the GLM models with estimates obtained using Generalised Estimating Equations (GEE).

Where necessary we will deal with multiple absorbing events (for competing risks) and left censoring. For all these models, either Population-averaged or marginal versus subject-specific or conditional survival probabilites will be estimated.

Equity effects will be examined by comparing differential effects on the primary outcomes between wealth tertiles and educational tertiles.

Although this is a large randomized trial and randomization will be constrained to achieve balance with respect to predictors of outcome, any remaining imbalances of predictors of the outcomes in question will be adjusted for in the regression models. In order to evaluate potential confounding, we will stratify the analyses on baseline characteristics that are or can be dichotomized, and if the stratified analyses give indications of confounding rather than effect measure modification, we will adjust the analyses for these baseline characteristic if their inclusion in the statistical model changes the effect estimate with more than 5% or substantially increases its statistical precision. For continuous variables such as age, we will also explore whether there is effect measure modification using appropriate interaction terms and, if not, adjust for variables using the criteria described above. For analysis where adjustment for several baseline characteristics turn out to be necessary, e.g. in (predefined) sub-group analyses, we will use statistical modelling approaches, such as those using the Akaike information criterion to arrive at a final model.

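### Adjustment covariates are chosen from the outcome data, so the primary estimate is not fixed in advance

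*Protocol*

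**What the plan says.** All of this is in one paragraph of the protocol's Statistical methods section. It gives three ways for a baseline factor to enter the effect model.

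- **Imbalance.** "any remaining imbalances of predictors of the outcomes in question will be adjusted for in the regression models". Neither the predictors nor what counts as an imbalance is stated.
- **Change in estimate or precision.** First, "we will stratify the analyses on baseline characteristics that are or can be dichotomized". The next step applies "if the stratified analyses give indications of confounding rather than effect measure modification". In that case the plan is to "adjust the analyses for these baseline characteristic if their inclusion in the statistical model changes the effect estimate with more than 5" per cent, or if the gain in precision is substantial. Age and other continuous factors are handled much alike: the plan will "explore whether there is effect measure modification using appropriate interaction terms and, if not, adjust for variables using the criteria described above".
- **Model selection.** Where several covariates are needed, with subgroup analyses as the example, the plan allows modelling approaches "such as those using the Akaike information criterion to arrive at a final model".

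The paragraph is not limited to secondary or exploratory analyses, and nothing in the protocol names an unadjusted or fixed-covariate estimate as primary. Under Randomization and blinding/masking, "Randomization will be stratified by district", but Statistical methods does not say that district enters the model.

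**The concern.** The stratified screen, the movement of the estimate, the gain in precision and the Akaike criterion are all computed from the outcome. The covariate set, and so the reported effect, depends on the results it is meant to summarise.

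Change-in-estimate rules come from observational work, where an estimate that moves may signal confounding. In a randomised trial baseline imbalance is chance, and the reason to adjust is that a covariate predicts the outcome. The rule also misreads some effect measures. The plan reports odds ratios and uses Cox regression, and both measures can move when a prognostic covariate is added even under perfect balance.

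At stake is whether the primary estimates are defined before the data are seen. The standard errors treat the chosen model as if it had been given in advance.

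**Working it through.** **1. Planning inputs reproduce.** From the Sample size table for birth before the 18th birthday (economic arm against control): rates 0.08 and 0.06 per year, 84 person-years per cluster, k = 0.15, z = 1.96, 80% power.

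c = 1 + (1.96 + 0.842)² × [(0.08 + 0.06)/84 + 0.15² × (0.08² + 0.06²)] / (0.08 − 0.06)² = 38.1, rounded up to 39. The table states 39. The covariate rule has no derived figure of its own, only the 5%.

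**2. What 5% means depends on the unstated scale.** With 31 control and 63 economic clusters:

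var(log RR) = [1/(0.08 × 84) + 0.15²]/31 + [1/(0.06 × 84) + 0.15²]/63 = 0.00553 + 0.00351 = 0.00903, so SE = 0.095.

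At the planned RR of 0.75:
- On log RR: 0.05 × 0.2877 = 0.0144, or 0.15 SE.
- On effectiveness (1 − RR): 0.05 × 0.25 = 0.0125, so RR 0.7375 or 0.7625. A log shift of ln(0.7625/0.75) = 0.0165 is 0.17 SE.
- On RR: 0.7125 or 0.7875, i.e. effectiveness 28.8% or 21.3%. A log shift of ln 1.05 = 0.049 is 0.51 SE.

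The same sentence sets thresholds that differ more than threefold (0.049/0.0144 = 3.4). The SE is only a yardstick here; step 4 shows how often chance crosses the threshold.

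**3. Number of models.** Three primary outcomes (Outcomes) times three pairwise comparisons (Statistical methods) give nine results, each open to its own set.

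**4. Simulation of the rule.** Poisson model with cluster-robust SE, 31 against 63 clusters of 28 girls, 1,500 trials per setting. Assumptions not in the protocol: six binary candidates, three of them prognostic with log rate ratio 0.3 or 0.7; covariate ICC 0.1; a substantial precision gain taken as a 5% fall in SE. The stratified screen is a judgement and is not part of the simulated rule.

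Share of trials in which at least one covariate enters:

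| True RR | 5% read on RR | 5% read on log RR |
|---|---|---|
| 0.75 | 1% to 50% | 44% to 95% |
| 1 | 1% to 57% | 93% to 99.9% |

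- Rejection at RR 1 (Monte Carlo error about ±1.2 points): rule 5.3% to 6.7%; unadjusted 5.3% to 6.2%; all six covariates always included 5.5% to 6.5%.
- Power at RR 0.75 (about ±2 points): unadjusted 80% to 81%; all six always included 81% to 87%. With the strong covariates the rule gave 82.9% (RR scale) and 85.3% (log scale), against 87.0% and 86.7% for the fixed set, a shortfall of 4.1 and 1.4 points. With the weak covariates on the log scale there was none (81.5% against 81.3%).
- The significance verdict under the rule differed from the unadjusted one in 0% to 10% of trials.
- Actual spread of the estimate divided by its mean reported SE, in six of the eight settings: 0.96 to 1.04 under the rule, 0.97 to 1.04 for the fixed set.

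**The case against.** The strongest reply is that the operating characteristics hardly suffer. Type I error under the rule cannot be told apart from the unadjusted analysis, and the reported standard errors are about as well calibrated as those of the fixed set. That stands, and it limits how heavily the point should weigh.

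It can also be said that naming covariates is ordinary SAP content. That would answer a silent protocol, but this one states the rule. A SAP that followed it would inherit the problem, and one that fixed the covariates would contradict it.

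Four stronger readings are tempting and not supported:

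- *Covariates enter only through the 5% or precision test.* The imbalance and Akaike routes are in the same paragraph. They are equally open.
- *Nearly any covariate qualifies when there is no effect, and few when there is one.* This depends on scale. On log RR or a risk difference the threshold shrinks towards zero with the effect. On RR it stays near 0.05 at the null, and the table shows almost no contrast (1% to 57% against 1% to 50%).
- *False positives rise to 7% or 8%.* A simulation reached that only by letting the analyst report the larger of the unadjusted and selected results. The plan does not permit this, so the figure measures selective reporting and not the rule.
- *The choice is made by unblinded analysts.* The protocol says that participants are not blinded and that efforts will be made to keep the final-survey team unaware of allocation. It is silent on the analysts.

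**Conclusion.** The point holds: the protocol fixes a data-driven selection rule for its main effect models and designates no primary estimate. The consequence is a primary result not defined in advance, with room for choice in the candidate list, the scale of the 5%, the precision threshold and the route, and possibly a little lost power. It does not show clear inflation of type I error. The entry rates and power figures rest on assumed covariate strengths and an assumed precision cut-off, so they illustrate a range and do not predict this trial. The conclusion that the model depends on the outcome data needs none of those assumptions. This is a free improvement, not an error that undermines the trial.

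**What to change.** Amend the covariate paragraph of Statistical methods, and any SAP, as follows.

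- State that the primary analysis of each primary outcome uses a prespecified covariate set: district, as the randomisation stratum, plus named baseline predictors. Age, household wealth and parental education are natural candidates where they were collected at baseline; the Outcomes section lists the last two as background information without giving a time point.
- Let the set differ between births and the grade 9 exam if wished, provided it is stated in advance and used for all three comparisons.
- Fix the set before any outcome data by arm are examined. Waiting until just before the final survey is too late, because the follow-up contacts record childbearing and schooling every six months.
- Report the model adjusted for district alone as a sensitivity analysis.
- Remove the confounding screen and the 5% and precision rule from the primary analysis. If change-in-estimate or Akaike selection is kept at all, label it exploratory.

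The cost is a protocol amendment and SAP wording. No additional data are needed, and none of the stated sample sizes changes, since they assume no covariate adjustment.

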## Cost-Benefit Analysis (CBA)

The cost benefit analysis will utilise trial outcomes and secondary data to calculate the Net Societal Benefits (NSB) of the intervention alternatives, using the following formula

$${{NSB}_{i}=\sum_{t=1}^{n} \frac{b_{i}\left( t \right)-c_{i}(t)}{{(1+r)}^{t-1}}}$$

Where,

NSB_i_ = Net societal benefit of the intervention for all girls *i* (discounted)

b_i_(t) = benefits (in monetary terms) associated with offering the intervention to girl *i* derived in year t

c_i_(t) = costs (in monetary terms) associated with offering the intervention to girl *i* in year t

1/(1+r) = discount factor on annual interest rate r

N = lifetime of the individuals

Benefits and costs will be estimated from the perspectives of the family, community, school, health care and the government, and from society as a whole. At the family level, benefits will be the cash transfers, reduced school-related costs for daughters, the value of improved health of daughter and her future children, reduced or delayed user fees and transport costs for health care services, and increased future income. The cost at family level will be delayed receipt of a bride price for the daughter. At the level of the local community there will be costs related to community members attending community meetings, and there will be benefits from increased productivity. At the health care level, there will be reduced costs if the need for health care decreases with a reduction in the number of premature or low birth weight babies, or if the morbidity is lower among children of women who have received the intervention. Prospective costing techniques will be used alongside the main trial to estimate costs of the intervention alternatives, while other trial outcomes will be valued and combined to estimate long term benefits. Valuation of health benefits will be based on incidence data from the trial combined with disease cost information from the literature. Differences in school attainment between the trial arms will be used to extrapolate long term educational outcomes, while its valuation in terms of increased future income at household level will be based on secondary data.

To assess whether cost-benefits are equitably distributed, we will do regression analysis, with NSB as dependent variable, and socio-economic status and intervention arm as independent variables.

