We have conducted two phases of formative research following the PRECEDE part of the model. Process evaluation was used in the pilot study and both process and end point evaluation will be utilized in the trial. The first phase of the formative research explored factors and processes that contribute to early childbearing and marriage and school dropout in the cultural and socioeconomic contexts of Monze, Mazabuka and Chikankata districts in Zambia. In-depth interviews (IDIs) and focus group discussions (FGDs) were conducted with girls, parents, teachers, health workers and community leaders in December 2014 and January 2015. The analysis of the qualitative interviews followed a classical approach employing Malterud’s ‘Systematic text condensation’ [34]. The social assessment revealed that the main explanations provided for school drop-out, early pregnancy and early marriage were overlapping and interlinked. Poverty was brought up as a reason for all three; many families cannot afford to buy uniforms or pay school fees at secondary level (primary school in Zambia is free, but secondary is not); parents may put pressure on their daughters to get sexual partners or to become pregnant to obtain the bride price and economic support for their daughters; and girls mentioned a desire for gifts/money as an important reason for having sex with a boyfriend. Pregnancy was described as leading to school drop-out and marriage, although some girls were reported to reenter school after having given birth. Several informants mentioned that many parents did not encourage their daughters to continue with school because they did not see the benefit of it, and instead encouraged them to get married. Girls being regarded as ready for marriage after menarche and school-dropout, and substantial social barriers to seeking contraceptives, were reported as other factors leading to girls getting pregnant. The latter is in line with reports from many Zambian districts indicating that youth friendly health services often exist only on paper, and that access to effective contraception for young girls may be limited because of the distance to health clinics, and because health care providers may express reluctance and moralistic dismay when young people seek contraceptives [13].

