| **Follow-up contacts** | All the girls in the intervention and control arms will be contacted every 6 months to update contact information and ask questions about school attendance, employment, marital status and childbearing, health care seeking, and whether they have received the cash transfers and/or participated in the youth club meetings. To monitor adverse events that can be attributed to the trial, girls will also be asked whether they have experienced problems due to their participation in the trial. In the fourth follow-up interview (taking place during the first two quarters of 2018) additional questions will be asked about communication about sexual and reproductive health issues.  In order to make it easier for the participants to respond to the more sensitive questions, Audio Computer Assisted Self-Interviewing (ACASI) will be used for questions 69-82. This will be done by giving the participants headsets so they can listen to the questions being read to them and they will be given privacy to fill in the correct responses on the tablets themselves. ACASI-technology has been shown to increase participants’ perceptions of privacy and anonymity and it appears to reduce social desirability bias [52, 53]. In addition, the item count technique [54, 55] will be used. This is an indirect questioning technique where the participants indicate how many of a set of statements are true for them, rather than whether each of the individual statements are true or false. If the girl cannot be found at school or at home at the time of the follow-up interview, call centre research assistants will attempt to reach her by phone.  In the third follow-up round we experienced challenges in several of the control schools with finding the participants because many of them were not in school any more. In order to motivate the participants to come to the school to be interviewed, we will increase the transport allowance provided for control participants from K20 to K50 per interview in 2018 and further to K75 in 2019 and K100 for the final interview in 2020. For the participants in the intervention arms, we do not think it is necessary to provide such an allowance during the period when they are receiving economic support, and thus a transport allowance of K75 / K100 will only be provided for interviews in 2019 and 2020. The participants will then have finished grade 9 and we expect a large proportion of them to move away from the study areas, either to go to grade 10 in a secondary school or to get married or work. This implies that they will either have to travel to come back for interviews and need to be compensated for the costs and time that this requires. And for those that move far away, they will have to keep their phone number active for us to be able to interview them over the phone and many of them will also have to call us to inform us when they will be available, and thus the compensation should be sufficient to cover the costs of this.  Around the time of the fourth follow-up interviews with the RISE participants in the first half of 2018, their parents/guardians will also be invited to come to parent meetings where they will be asked take part in an interview. Parents/guardians who do not come to the meeting will be sought at home. The questions in the parent interview pertain to expenses they have had in the previous 6-12 months related to food, education, health care and other expenditures, and about their attitudes to early marriage, early childbearing, contraceptive use and education. A travel allowance of K50 will be offered to the guardians who are interviewed.  The research assistants will be asked to take selfies of themselves with the participants to document that they have interviewed the correct participants. The trial participants in most cases live far away from each other and the research assistants who do the interviews travel alone (or with a driver) on a motorbike to find the participants. Thus, even if there is a supervisor who makes unannounced monitoring visits to observe the research assistants twice per month, most of the interviews are done without other project staff being able to observe them. We are worried that some of the research assistants may be tempted to manufacture some of the interviews, particularly when it is difficult to find participants because they have moved (which is the case for an increasing proportion of our participants). We expect that such pictures will make fabrication of interviews less likely. |

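### The cost-benefit plan credits income from extrapolated schooling but names no family cost for the unsupported school years; applied as written, it would overstate net benefit

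*Protocol*

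**What the plan says.** All of the economic plan is in the protocol section Cost-Benefit Analysis (CBA). It sums discounted benefits minus costs for each girl over a horizon given as "N = lifetime of the individuals". The cost term is general: "costs (in monetary terms) associated with offering the intervention to girl *i* in year t". The scope is wide: "Benefits and costs will be estimated from the perspectives of the family, community, school, health care and the government, and from society as a whole".

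The section then lists items. The family's benefits include lower school costs and higher future income. The family's cost is stated in one sentence: "The cost at family level will be delayed receipt of a bride price for the daughter". Intervention costs have their own source: "Prospective costing techniques will be used alongside the main trial to estimate costs of the intervention alternatives". For the long run, "Differences in school attainment between the trial arms will be used to extrapolate long term educational outcomes", and the extra schooling is valued as future household income from secondary data.

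Four other places bear on this:

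- Interventions, 'Economic support' arm: project fee payment is for grades 8 and 9.
- Interventions, opening paragraph: support ends in November 2018, when girls still in school are expected to finish grade 9.
- Preparatory work: "primary school in Zambia is free, but secondary is not".
- Secondary outcomes, School-related, and Table 1 (Follow-up contacts): grade 10 enrolment is an outcome, and many girls are expected to move away after grade 9, "either to go to grade 10 in a secondary school or to get married or work".

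**The concern.** Extrapolating attainment means projecting school years that the project does not pay for. The income from those years is credited to the family, but the fees, materials, transport and boarding needed to obtain it appear nowhere in the family's cost line. The only schooling entry in that account is a saving, which fits the years when the package pays but not the years after it.

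Cost-benefit is part of both primary objectives, and the second asks whether the combined intervention is more cost-beneficial than economic support alone. A cost that grows with the education effect does not cancel between arms, so leaving it out favours the arm that keeps more girls in school. NSB is also the dependent variable in the planned equity regression, so any error would carry over there.

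**Working it through.** The protocol states no NSB, no cost per school year, no income gain and no numeric discount rate, so there is no economic figure to reproduce. The check has two parts: the items as listed, and the scale of the missing item under stated assumptions.

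**1. Items listed in the CBA section**

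| Level | Benefits named | Costs named |
|---|---|---|
| Family | cash transfers, lower school costs, better health, less or later spending on care, higher future income | delayed bride price |
| Community | productivity | attending meetings |
| Health care | lower care costs | none |
| School | none | none |
| Government | none | none |

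Intervention costs are added by prospective costing. No listed item covers the family's spending on school after support ends.

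**2. Timing.** Girls are in grade 7 in 2016. Taking 2016 as t = 1, a girl on schedule finishes grade 9 in 2018 (t = 3) and would be in grades 10 to 12 at t = 4, 5 and 6, all after the last fee payment.

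**3. Planned education effects (Sample size, grade 9 exam table).** Control 0.70, economic 0.805, combined 0.886.

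- Economic minus control: 0.805 - 0.70 = 0.105, or 10.5 per 100 girls.
- Combined minus control: 0.886 - 0.70 = 0.186, or 18.6 per 100 girls.

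These are the values behind the plan's own calculation. With 28 girls per cluster, ICC 0.02 (design effect 1 + 27 × 0.02 = 1.54) and 95% power, they give 24.0 clusters per arm for economic vs control, 28.3 for combined vs economic and 6.7 for combined vs control. The plan states 24, 29 and 7.

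**4. Scale of the missing item**, using the plan's own discounting:

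excess NSB per girl = d × q × A(r) × S, with A(r) = Σ 1/(1+r)^(t-1) over t = 4, 5, 6.

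Here d is the arm difference from step 3. Three inputs are assumptions: q, the share of the extra exam sitters who go through grades 10 to 12 (0.25 to 1); r, the discount rate (0, 3% or 10%); and S, the annual schooling cost left out.

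- A(0) = 3
- A(0.03) = 0.915 + 0.888 + 0.863 = 2.666
- A(0.10) = 0.751 + 0.683 + 0.621 = 2.055

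Excess NSB in ZMW per girl offered the intervention, for S = ZMW 1000:

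| q | Economic: r = 0 / 3% / 10% | Combined: r = 0 / 3% / 10% |
|---|---|---|
| 0.25 | 79 / 70 / 54 | 140 / 124 / 96 |
| 0.5 | 158 / 140 / 108 | 279 / 248 / 191 |
| 1.0 | 315 / 280 / 216 | 558 / 496 / 382 |

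The low end for the economic arm, for example, is 0.105 × 0.25 × 2.055 × 1000 = 54; the high end is 0.105 × 1 × 3 × 1000 = 315. In combined vs economic, the net advantage to the combined arm is 96 - 54 = 42 up to 558 - 315 = 243 per ZMW 1000.

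The result is proportional to S. Over an assumed S of ZMW 500 to 3000, the full range is ZMW 27-945 (economic) and 48-1,674 (combined) per girl. If only the family's share of the cost is left out, S is that share alone.

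**The case against.** The strongest reply is that the plan does not exclude these costs. The cost term is general and runs over the lifetime, and the school, government and societal perspectives are all named. Nothing is itemised at school or government level on either side, and that detail may sit in a separate analysis plan. This stands. A reader might infer that nobody is charged for the extra schooling, or that teaching costs are omitted; the text does not support either.

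Four further points have force:

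- The sentence on prospective costing does not say it is the only cost source, and the section also draws on secondary data.
- That the extrapolation runs past grade 9 is an inference. It is a reasonable one, since the text speaks of long-term outcomes and grade 10 enrolment is measured, but it is not stated.
- The school-cost saving carries no dates. A reader might infer that it is applied with the wrong sign to later years; it may be meant only for the period when the package pays.
- The income figure from secondary data could already be net of schooling cost, and the protocol reports a government aim, of uncertain timing, to make secondary education free.

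What the reply does not remove is the explicit family-cost sentence. It is a stated item, not silence, and a general symbol in the formula does not add a second item to it.

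**Conclusion.** The point holds for the family account. Delayed bride price is the named family cost, schooling enters only as a saving, and income from extrapolated attainment is credited. Applied as written, NSB would be overstated, more in the arm with the larger education gain. The direction follows from the structure: d is positive on the planned effects, and so are q, A(r) and S.

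The size cannot be derived from the documents. The illustration in ZMW rests on assumed progression, discount rate and unit cost, and on the extra exam sitters being the only source of an arm difference in grades 10 to 12. It also does not show that the sign of NSB or the ranking of the arms would change, because there is no NSB figure to compare it with. It would therefore go too far to say that the net benefit is overstated as a matter of fact. For the school and government levels the protocol is only unspecific. The correction is worth making because it touches the cost-benefit part of both primary objectives; the birth and exam outcomes are unaffected.

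**What to change.** In the Cost-Benefit Analysis section:

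1. Replace the single family cost with two: delayed bride price, and the direct family cost (fees, materials, transport, boarding) of every school year credited in the extrapolated education benefit, entered in c_i(t) in the year it falls.
2. Limit the family's school-cost saving to the support period, 2016-2018.
3. State that the recurrent public cost per pupil, net of fees, for the same school years enters under the school and government perspectives already named.

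For data, use the education spending that guardians report in the 2018 interviews (Table 1, Follow-up contacts). Those interviews fall within the support period, so spending in the intervention arms is subsidised and control families give the unsubsidised figure. Grades 10 to 12 need secondary data, which the section already plans to use.

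The cost is a few sentences, one unit-cost input with a sensitivity range, and a little more analysis work. No new data collection is needed. The reported NSB becomes less favourable.
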